### 8.1.1 Assignment of subject ID code

The investigator or subinvestigator will assign a subject ID code to a subject from whom the written consent for study participation has been obtained. The subject ID code will be assigned based on the following rules.

Subject ID code: 7580-005-XX-YY

XX: Investigative site number (see Attachment 1 in the protocol [separate volume])

YY: Serial number of subjects from whom the consent for study participation has been obtained at the concerned investigative site.

Example) When informed consent is obtained for the first time at ⚫⚫ Hospital (Investigative site number: 01), subject ID code will be 7580-005-01-01.

The investigator or subinvestigator will record the subject ID code in the screening roster when assigning a subject ID code.

## 8.2 Enrollment Procedures

Study subjects will be enrolled according to the following procedures.

1) The investigator or subinvestigator will conduct the screening according to “[9](#_9_Observation,_Examination,) Observation, Examination, Test Items and Implementation Schedule” after obtaining informed consent. Retest may be repeated twice for the inclusion criteria 4), 5) and exclusion criterion 7).

2) The investigator or subinvestigator will confirm all the inclusion and exclusion criteria, and prepare “Case Registration Form for Phase II Study of KHK7580” (see Attachment 3 in the protocol [separate volume]) for all the subjects from whom informed consent was obtained irrespective of the applicability of the criteria, and send it via facsimile to 7580-005 Registration Center. Enrollment will be carried out after the date of determining the result of all inclusion and exclusion criteria (after finding out the screening results) and before administration of the investigational product on Day 1. However, when a subject withdraws consent or is found to be ineligible after obtaining the informed consent, “Case Registration Form for Phase II Study of KHK7580” may be prepared at that time and sent to 7580-005 Registration Center via [contact] Registration Center will check the eligibility of subjects, and send “Registration Confirmation Form for Phase II Clinical Study of KHK7580” to the investigator or subinvestigator via facsimile when eligibility is confirmed. In the case the contents of registration are unclear, 7580-005 Registration Center (or the sponsor who was contacted) may make inquiries to the investigator, subinvestigator, or the Sponsor. A subject who does not meet the inclusion criteria and/or meet the exclusion criteria will be specified as ineligible in the “Ineligibility Conformation Form for Phase II Clinical Study of KHK7580,” which will be sent to the investigator or subinvestigator via facsimile. The investigator or subinvestigator will input the reason for ineligibility to the electronic case report form.

4) The investigator or subinvestigator will record the enrolled subject in a screening roster and store it.

The enrolment procedure is summarized below.

Investigator or subinvestigator

7580-005 Registration Center

➀ Selection of subjects

Checking subject demographics.

➁ Obtaining informed consent and assigning subject ID code

Explain the clinical study, obtain written. informed consent, and assign subject ID code.

➂ Screening

Confirm eligibility by conducting screening.

➃ Registration

“Case Registration Form” will be sent to 7580-005 Registration Center via facsimile before administration of the investigational product on Day 1.

➅ Checking registration

Prescribe the instructed IP by checking the “Registration Confirmation Form.”

➄ Checking eligibility and feasibility of registration, and allocation of the subjects

When a subject is judged eligible after checking eligibility, IP will be allocated, and “Registration Confirmation Form” containing the drug number and necessary items will be sent to the investigator or subinvestigator via facsimile.

When a subject is judged ineligible, “Ineligibility Confirmation Form” will be sent to the investigator or subinvestigator via facsimile.

# 9 Observation, Examination, Test Items and Implementation Schedule

## 9.1 Implementation Schedule

All examinations stipulated during the investigational product administration period will be performed prior to investigational product administration and prior to the start of dialysis, except for 1 hour and 3 hours after administration on the day of starting administration (Day 1). Except for screening and the ophthalmologic examination and carotid ultrasonography stipulated on Day 22 and Day 29, all tests will be performed prior to the start of dialysis, but this restriction will not apply to assessment upon discontinuation.

The following range will be permitted for hospital visits.

• Day 3, 5, 8, 10, 12, 15, 17, 19, 22, 29: ± 1 day

Assessments upon discontinuation will be performed as soon as possible after the subject discontinued the study.

Table 9.1-1 Observation, examination, and test schedule

[figure not shown]

a: The date of dialysis after the longest interval between dialysis sessions will be used.

b: Performed from the day of completion of eligibility confirmation for all of the inclusion and exclusion criteria until pre-dose of investigational product on Day 1.

c: Performed from the time of acquisition of consent until pre-dose of investigational product on Day 1.

d: Only AST and ALT will be used. If the test value meets exclusion criterion 7), up to two retests will be permitted.

e: Only intact PTH, corrected serum Ca, Ca, and Alb will be used. If the values do not correspond to inclusion criteria 4) and 5), up to two retests will be permitted.

f: Blood will be only collected from subjects assigned to the KHK7580 0.5, 1, 2 mg, or placebo group.

g: Food intake will be prohibited from investigational product administration until the completion of blood sampling 3 hours after the administration.

h: Females only. However, no test will be required if at least 12 months have passed since the subject’s last menstruation in the absence of any other medical cause.

i: Performed within 14 days after Day 22.

j: Blood will be only collected from subjects assigned to the KHK7580 0.5, 1, 2 mg, or placebo group and who have consented to the storage and use of blood samples.

k: Prohibited concomitant medications and restricted concomitant medications will be checked from the date of screening, and other concomitant medications will be checked from Day 1.

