| TRACP-5b | Tartrate-resistant acid phosphatase 5b |
| Adverse Reaction | Any adverse event for which the causal relationship to the investigational product was assessed as “related” or “unknown.” |

Study period

The study period for each subject is defined as the period from the acquisition date of informed consent to the stipulated final assessments or assessments upon discontinuation.

Investigational product administration start date, time since administration

Investigational product administration start date was Day 1. The time elapsed after investigational product administration was described as X hours after investigational product administration.

End of investigational product administration

Day 22 or upon discontinuation prior to Day 22.

SUMMARY OF STUDY PLAN

I Objectives

The objective of this study was to evaluate the efficacy and safety of 0.5, 1, or 2 mg KHK7580 or placebo, or 25 mg KRN1493 (cinacalcet hydrochloride) orally administered to subjects with secondary hyperparathyroidism (SHPT) receiving hemodialysis (HD) once daily for 3 weeks in a multicenter, randomized, placebo-controlled, double-blind, parallel-group, dose-response study (including the KRN1493 group as an open-control group).

II Study Phase

Phase 2

III Criteria for Evaluation

1) Efficacy Evaluation

Primary Endpoint:

• Percent change in intact PTH level from baseline at the end of study treatment

Secondary Endpoints:

• Number and percentage of subjects achieving a percent decrease in intact PTH level of ≥30% (percent change ≤−30%) at the end of study treatment

• Number and percentage of subjects achieving an intact PTH level of ≤240 pg/mL at the end of study treatment

• Intact PTH level, whole PTH level, corrected serum Ca level, ionized Ca level, serum P level, intact fibroblast growth factor-23 (FGF23) level, and corrected serum Ca-P product at each time point and at the end of study treatment

Exploratory Endpoints:

• Bone metabolic markers at the end of study treatment and at the end of the follow-up period

• Parathyroid gland (volume and blood flow) at the end of study treatment

2) Safety Evaluation

• Treatment-emergent adverse events (TEAEs)

• Lowest corrected serum Ca level between the start of study treatment and the end of the follow-up period

• Laboratory values

• Vital signs

• 12-lead electrocardiogram

• Ophthalmological examination

3) Pharmacokinetic Evaluation

• Plasma KHK7580 concentration

IV Subjects (Disease)

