## 9.3 Observation and Examination Items and Timing of Implementation

### 9.3.1 Exposure Investigation

The administration date and administration status of the investigational product will be investigated.

Timing of implementation:

From the date of starting investigational product administration (Day 1) to the date of completion of investigational product administration (Day 21).

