# 12 Discontinuation Criteria and Procedures

## 12.1 Discontinuation of a Relevant Subject

### 12.1.1 Discontinuation criteria

If any of the following criteria is met after enrollment, the study will be discontinued for the subject in question.

1) The subject is found to be ineligible because enrollment criteria are not met.

2) The subject asked to discontinue the study.

3) It is found not to be feasible to conduct necessary observations and tests because of the subject’s private reasons.

4) The investigator or subinvestigator determines that the subject should be discontinued from the study because of the occurrence of an adverse event.

5) Corrected serum Ca level decreased to ≤7.5 mg/dL.
If deemed necessary, the investigator or subinvestigator is to give appropriate treatment such as intravenous infusion of a Ca preparation as required in the event of discontinuation for this reason.

6) Other situations where the investigator or subinvestigator determines that the subject should be discontinued from the study.

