# 13 Endpoints

## 13.1 Efficacy

### 13.1.1 Primary endpoint

• Intact PTH level change rate at the end of investigational product administration

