## 14.5 Handling of Missing, Unused, and Abnormal Data

Data for the analyses shown in Section [14.1](#_14.1_Statistical_Methods) will be handled as shown below. If data that are inconsistent with this are obtained, or handling needed to be reviewed for each subject because of an unexpected event at the start of the study initiation, a decision on handling will be taken before the database lock.

1) If any data are missing at the end of investigational product administration during summarization for the primary endpoint and secondary endpoints, data in the data obtained from after investigational product administration until the end of investigational product administration will be supplemented by Last Observation Carried Forward (LOCF) using data from the final time point as the investigational product administration end time.

2) Binary response variables such as the secondary endpoint “Achievement of an intact PTH level of ≤240 pg/mL at the end of investigational product administration” will be handled as non-achieving subjects if the investigational product administration end time is missing.

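### For early stoppers, the primary-endpoint PTH is a discontinuation sample that need not be pre-dialysis, near the last dose, or before calcium treatment

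*Protocol*

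**What the plan says.** - Section 13.1.1 gives the primary endpoint as "Intact PTH level change rate at the end of investigational product administration". Section 14.1.1.1 measures it from the pre-dose value on Day 1.
- The Definitions of Terms set the end of administration at "Day 22 or upon discontinuation prior to Day 22".
- Section 9.4.1.3 schedules intact PTH on Day 1 before dosing, on Days 3, 5, 8 and 15 before dosing and dialysis, on Days 22 and 29 before dialysis, and at discontinuation with no condition attached. By section 7.1 the first dose is taken just before dialysis, so the baseline is also pre-dialysis.
- Section 9.1 states the sampling rule with its exception, "all tests will be performed prior to the start of dialysis, but this restriction will not apply to assessment upon discontinuation", and the timing: "Assessments upon discontinuation will be performed as soon as possible after the subject discontinued the study".
- Section 12.1.1 lists corrected calcium of 7.5 mg/dL or lower as a reason to stop. If deemed necessary, the investigator is to "give appropriate treatment such as intravenous infusion of a Ca preparation as required in the event of discontinuation for this reason". Section 12.1.2 asks for prompt examinations but sets no order between treatment and sampling.
- Section 14.5 applies LOCF only when the end value is missing, "using data from the final time point as the investigational product administration end time". It sets no condition on how that value was sampled.
- Section 14.7.2 makes the PPS the principal efficacy set and drops subjects below 70% of a fixed 21 tablets. Section 14.7.1 gives the FAS a supporting role.

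**The concern.** A percent change is interpretable only if both of its values are taken under like conditions. Here the baseline and the completers' end value are pre-dialysis, while a stopper's end value is released from that condition by an explicit rule.

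The Protocol itself treats these conditions as relevant to efficacy. Section 7.2.2 freezes calcium preparations and dialysis conditions, and section 25.6 says this is for a proper evaluation of efficacy and safety. Section 1.1 describes low calcium as a stimulus to PTH secretion, so treatment that raises calcium acts on the measured variable. Time off drug matters as well, because the drug works by suppressing PTH.

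The affected subjects are unlikely to be spread evenly over the groups. In the earlier patient study (section 1.4.3), blood calcium decreased was an adverse reaction in 8 of 24 patients on repeated 4 mg, and 3 of them discontinued. If such stops cluster at the higher doses, the distortion falls unequally on the group means that the dose-response contrasts compare.

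**Working it through.** **1. Sampling conditions side by side**

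| Value | Before dialysis? | Time since last dose | Relation to calcium treatment |
| --- | --- | --- | --- |
| Baseline, Day 1 | Yes (7.1, 9.4.1.3) | Before first dose | Calcium preparations frozen (7.2.2) |
| Completer, Day 22 | Yes (9.4.1.3) | Last dose Day 21 (9.3.1), visit within ±1 day | Calcium preparations frozen (7.2.2) |
| Early stopper, discontinuation | Not required (9.1) | No maximum set (9.1) | Order not set (12.1.1, 12.1.2) |

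The third row supplies the primary-endpoint value through the definition of end of administration. Because that value is present, LOCF does not come into play.

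**2. Who reaches the principal analysis**

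Compliance = 100 × tablets taken / 21. For 14 tablets, 100 × 14/21 = 66.7%, excluded. For 15 tablets, 100 × 15/21 = 71.4%, included.

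At one tablet a day, a subject stopped at the Day 15 pre-dose draw has taken 14 tablets and leaves the PPS. Stops prompted by the Day 3, 5 or 8 draws leave it too, unless dosing runs on for about a week or more. What remains is mainly week-3 stoppers. An example is a low Day 15 calcium reported by the central laboratory (9.4.1) after that day's dose; the reporting delay is my assumption. The FAS takes every early stopper with a baseline and any later PTH.

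**3. The plan's own power figure**

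Inputs from section 25.12: means 0, −6.71, −13.42 and −19.80; SD 22.47; 28 per group; about 90% power. The interpolated means reproduce: −13.42/2 = −6.71, and −13.42 + (−32.57 + 13.42)/3 = −19.80.

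For each contrast in Table 14.1.1.1-1, t = Σcᵢȳᵢ / √(s² Σcᵢ²/n), and the test uses the largest |t| of the seven. With simulated normal data, the two-sided 5% critical value is 2.44; a simulated null stood in for the permutation step. Power over 60,000 simulated trials is 0.902, so the stated figure holds.

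**4. Illustration of size (assumed shares and shifts)**

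Movement of the 2 mg mean = share affected × shift. Only the 2 mg group is affected, each subject independently, with 28 per group.

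| Share | Shift, points | Mean moves by | Power, PTH too high | Power, PTH too low |
| --- | --- | --- | --- | --- |
| 1/30 | 20 | 0.67 | 0.880 | 0.916 |
| 1/30 | 40 | 1.33 | 0.852 | 0.926 |
| 2/30 | 20 | 1.33 | 0.858 | 0.929 |
| 2/30 | 40 | 2.67 | 0.794 | 0.944 |
| 12.5% | 20 | 2.50 | 0.813 | 0.948 |
| 12.5% | 40 | 5.00 | 0.680 | 0.970 |

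The last share is 3/24 = 12.5%, the low-calcium discontinuation rate at 4 mg. That is twice the top dose here and counts stoppers at any time, so I take it as an upper bound. The power gains in the right-hand column are bias, not benefit.

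**The case against.** The strongest reply is that the principal analysis is largely shielded. The 21-tablet denominator removes most stoppers from the PPS, and the FAS only supports it. This stands, and it limits the reach.

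Next, the choice of sample and window is ordinary SAP content, section 14.5 allows unexpected cases to be settled before database lock, and section 14.7.2 can exclude major violations. This carries less weight. The Protocol is not silent: it states which sample is the end value and exempts it from the sampling rule. A sample that follows the Protocol is neither unexpected nor clearly a violation.

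The shifts are assumed, and no section says how far dialysis moves PTH. That stands too.

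A reader might also infer stronger points that the documents do not support:

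- That the sample follows intravenous calcium. The text only fails to exclude this. Such treatment is given if deemed necessary, and examinations are to be prompt.
- That the bias has a known sign. Time off drug would raise PTH and added calcium would tend to lower it, so the net direction is open.
- That being off drug by itself sets stoppers apart. Completers' Day 22 sample also follows the last dose; the difference is that stoppers have no maximum interval.
- That completers share the fault because Day 22 may fall a day late ("Day 3, 5, 8, 10, 12, 15, 17, 19, 22, 29: ± 1 day"). That is a stated, narrow window. No PTH is scheduled between Days 15 and 22, so discarding a late value would swap a three-week result for a two-week one.
- That Day 21 in section 9.3.1 contradicts Day 22 in the definitions. The first is the last dose, the second the assessment.

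**Conclusion.** The point holds for early stoppers only. Their primary-endpoint PTH is a sample expressly freed from the pre-dialysis condition, with no limit on time since the last dose and no required order relative to calcium treatment, while baseline and Day 22 values are pre-dialysis.

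In the principal analysis it concerns stoppers with at least 15 of 21 tablets, probably few; in the FAS it concerns all early stoppers with a PTH value. With 1 affected subject in 30, the 2 mg mean moves by 0.67 to 1.33 points, or 3% to 7% of 19.80, and power lies between 0.85 and 0.93 against 0.902. At the upper-bound share, the mean moves by 2.5 to 5.0 points (13% to 25%), and power lies between 0.68 and 0.97 depending on direction. These figures rest on assumed shifts and on placing all affected subjects in the 2 mg group. That low-calcium stopping is dose-related is likely but not shown for these doses.

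**What to change.** In section 14.5, for early stoppers only, state that the discontinuation PTH serves as the end-of-administration value if it was drawn before dialysis, within a stated short interval of the last dose, and before any calcium treatment for the event. Otherwise use the last scheduled pre-dialysis on-treatment PTH. Report a sensitivity analysis that uses the discontinuation sample throughout. Say also what happens when a stopper has no earlier on-treatment PTH; keeping the discontinuation value and flagging it would leave FAS membership unchanged. Completers keep their Day 22 ±1 day value.

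The cost is a few sentences. Dosing dates (9.3.1), dialysis dates and start times (9.3.2) and calcium use (7.2) are already collected; the time of the draw relative to dialysis and calcium treatment must be available at discontinuation. The downside is that a few stoppers' end values come from an earlier visit, usually Day 15 for those who remain in the PPS. No visit, dose, stopping or treatment rule changes; only the choice of sample for analysis does.

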## 9.2 Subject Demographic Information

The following items will be surveyed:

Acquisition date of written consent, date of birth, sex, concurrent diseases, medical history, primary disease, year and month of dialysis initiation, history of PTx and year and month of PTx, history of parathyroid intervention and year and month of parathyroid intervention, dialysis conditions (dialysate Ca level, dialysis status in routine clinical practice, dialyzer, dry weight, prescribed blood flow, prescribed dialysate flow rate, dialysis efficiency*), status of use of cinacalcet hydrochloride or other calcimimetics, current smoking habit, and other items related to the inclusion and exclusion criteria

Timing of implementation: At screening.

* Data obtained on the day of screening or the latest data before screening will be used (data prior to acquisition of consent can also be used).

## 9.3 Observation and Examination Items and Timing of Implementation

### 9.3.1 Exposure Investigation

The administration date and administration status of the investigational product will be investigated.

Timing of implementation:

From the date of starting investigational product administration (Day 1) to the date of completion of investigational product administration (Day 21).

### 9.3.2 Dialysis Status Investigation

The date and start time of dialysis will be investigated. The details and reason for any changes in dialysis conditions will also to be investigated.

Timing of implementation:

From the date of starting investigational product administration (Day 1) to the date of completion of follow-up observation (Day 29).

## 9.4 Test Parameters and Timing of Implementation

### 9.4.1 Laboratory Tests

Laboratory tests will be performed according to the specified test schedule to check for any variation in laboratory values since investigational product administration. All laboratory values will be determined by a central laboratory, and measurements will be reported to the Sponsor.

#### 9.4.1.1 Hematology

Parameters:

WBC, differential white blood cell count, RBC, Hb, Ht, PLT

Timing of implementation:

• Day 1 (prior to investigational product administration)

• Day 8, 15^*^ (prior to investigational product administration and prior to start of dialysis)

• Day 22, 29^*^ (prior to start of dialysis)

• Discontinuation

* When the central laboratory is closed, the tests of Day 8 and 15 may be conducted on Day 5 and 12, respectively. The tests of Day 29 may be conducted within 7 days.

#### 9.4.1.2 Blood biochemical tests-1

Parameters:

T-Cho, TG, TP, BUN, UA, Cr, T-Bil, AST, ALT, γ-GTP, LDH, ALP, CK, ChE, Na, K, Cl, Mg, calcitonin

Timing of implementation:

• At screening^*1^ (prior to start of dialysis)

• Day 1 (prior to investigational product administration)

• Day 8, 15^*2^ (prior to investigational product administration and prior to start of dialysis)

• Day 22, 29^*2^ (prior to start of dialysis)

• Discontinuation

*1: Only for AST and ALT.

*2: When the central laboratory is closed, the tests of Day 8 and 15 may be conducted on Day 5 and 12, respectively. The tests of Day 29 may be conducted within 7 days.

